##### Objective recovery

Objective recovery will be assessed using the Social Functioning Scale [48]. Mueser defines social and role functioning as aspects of objective recovery. Both are covered with this scale, which has 19 items and the following seven dimensions: social withdrawal, relationships, social activities, recreational activities, independence (competence), independence (performance), and employment. This scale has been described as reliable, valid, sensitive and responsive to change.

#### Cost-utility

The number and duration of outpatient treatment contacts and inpatient days will be calculated in cost in Euro’s. They are related with changes in quality of life measured with the EQ-5D [39]. Cost-utility can be calculated by transforming scores on the EQ-5D into so-called QALYs [49]. To calculate cost-utility, only the cost of health care consumption is included, not social costs such as rent, benefits, etc.

### Blinding

Thirteen of the above scales are self-report scales, and two (IMRS-clinician version and SES) will be rated by non-blinded clinicians who will not be involved in the IMR training. Granholm’s Goals Template will be rated by the blinded research assistants in an interview with the clinician.

At the second and third measurements, the measurement procedure will be single-blinded: the research assistants will not know whether a client is participating in the experimental condition or the control condition; this procedure will preclude experimenter’s bias. To ensure this, clients and clinicians alike will be instructed before the interview not to inform the interviewer in any way about the client’s condition. At the end of each interview, interviewers will answer the question whether they have found out which condition the clients are in.

### Sample size

On the basis of the effect sizes of the studies by Hasson-Ohayon et al. (2007), Levitt et al. (2009) and Färdig et al. (2011) [16–18], we anticipate a medium effect size of 0.40 on the primary outcome variable (self-rated IMR scale, Mueser et al. 2004, 2005 [23, 24]). On the basis of the power analyses with three times of measurement (mixed models), equal allocation to the experimental and control groups, a power of .80, alpha at 0.05, and an effect size of .40, it will be necessary to randomize 148 clients: 74 to the experimental condition and 74 to the CAU group [50, 51].

### Randomisation

Because IMR is a relatively long-term care programme—in our pilot study at least 8 months at one session per week—the drop-out from treatment may be relatively high. Other studies had 29 % [17], 15 % [18]; 51 % [20], and 72 % [15]. Due to the 50 % drop-out rate expected from treatment in the experimental condition (a pessimistic estimate), we have chosen to allocate more clients to the experimental condition (IMR) than to the CAU group (proportions of 3:2). We will randomise 200 clients (on the basis of a conservative calculation): 120 to the experimental condition and 80 to the CAU group.

Randomisation will be stratified by team. To ensure the right distribution of clients per team in the two groups, envelopes containing five lots per team will be used each time. For this we will use a randomisation plan from http://www.randomization.com. After completing the baseline interviews, the principal investigator will allocate participants to the experimental group or control group.

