#### Recruitment procedure

Participants will be recruited from 14 community mental health teams at 11 branches of two mental health institutions in the greater Rotterdam area (the Netherlands). Eight teams throughout the city of Rotterdam serve an urban area of approximately 1.2 million inhabitants, one team serves a more rural environment to the west of Rotterdam, and five teams serve the neighbouring city of Dordrecht (120,000 inhabitants) and four smaller communities of 20,000–35,000 inhabitants.

During interviews with an assistant researcher, the caseloads of all clinicians in these teams will be assessed for their potential suitability for IMR. The clinicians will ask selected clients to participate in IMR and about their willingness to be informed about the study. If clients express interest and agree to be contacted by an assistant researcher for more detailed information, the assistant researcher will explain the research goals, randomisation procedure and the three times of measurement. Clients will then be asked whether they want to participate in the study. After written informed consent has been given, the baseline interview will be followed by randomisation.

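### One fixed block size of five per team, with the principal investigator allocating, makes up to 30% of allocations certain in advance to anyone who knows the block size and the team's tally

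*Protocol article*

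**What the plan says.** All references are to the protocol article.

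- **Randomisation, ratio and size:** clients are allocated in "proportions of 3:2", that is "120 to the experimental condition and 80 to the CAU group".
- **Randomisation, strata and blocks:** "Randomisation will be stratified by team", and to get the intended split within each team "envelopes containing five lots per team will be used each time". No other set size is mentioned.
- **Randomisation, source and allocator:** "we will use a randomisation plan from http://www.randomization.com". Once baseline interviews are done, "the principal investigator will allocate participants to the experimental group or control group".
- **Recruitment procedure:** "Participants will be recruited from 14 community mental health teams at 11 branches". An assistant researcher goes through every clinician's caseload for suitable clients. Then: "The clinicians will ask selected clients to participate in IMR and about their willingness to be informed about the study". Consent and the baseline interview come before randomisation.
- **Blinding:** the research assistants are blinded at the second and third measurements. The clinicians who rate two of the scales are not, and clients and clinicians are asked not to reveal the condition, so both know it.
- **Limitations:** the article accepts that clinicians might favour some of their clients, such as the better-functioning ones, even though they are meant to ask everyone selected.

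**The concern.** A small block of constant size within a small stratum runs out in a predictable way. Once three IMR lots or two CAU lots of a set are used, the rest of that set is known. The allocator holds the block size and the running tally and so needs no inference. Clinicians learn the arms of their own clients, decide when to raise the study with a client, and by the article's own account may have favourites.

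As the article describes it, that preference is a recruitment bias, which affects whom the results apply to. If upcoming slots can be foreseen, the same preference can become a difference between the arms, which affects whether the comparison is valid. The primary outcome is rated by clients who know their arm. The longitudinal model takes account of measured baseline scores, but it cannot remove selection on unmeasured traits such as motivation.

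**Working it through.** **Inputs.** Set size 5, ratio 3:2, stratification by team, 200 clients and 120/80 (Randomisation); 14 teams (Recruitment procedure). Assumptions: each set holds three IMR and two CAU lots, lots are drawn one at a time, and the observer knows the set size and all earlier draws in the team.

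**The plan's own split.** 200/5 = 40 sets; 40 × 3 = 120 IMR and 40 × 2 = 80 CAU. This matches the stated figures and supports reading each set as a 3:2 block.

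**Enumeration.** There are C(5,3) = 10 equally likely orders of three IMR and two CAU lots. A draw is certain when only one arm's lots remain. The best guess is the arm with more lots left, with ties counted as 0.5.

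| Position in block | 1 | 2 | 3 | 4 | 5 | Sum |
|---|---|---|---|---|---|---|
| Probability that the draw is certain | 0 | 0 | 0.10 | 0.40 | 1.00 | 1.5 |
| Probability that the best guess is right | 0.60 | 0.60 | 0.70 | 0.70 | 1.00 | 3.6 |

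- Position 3 is certain only if both CAU lots came first (1 order of 10). Position 4 is certain if the first three draws were all IMR (1 of 10) or included both CAU lots (3 of 10).
- Certain: 1.5/5 = 30%. Correct guesses: 3.6/5 = 72%, against 60% from always guessing IMR.
- Cross-check for a block with a IMR and b CAU lots: expected certain draws = a/(b+1) + b/(a+1) = 3/3 + 2/4 = 1.5. The first term is the known IMR slots, 1.0 of 5 (20%). The second is the known CAU slots, 0.5 of 5 (10%).

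**Number of clients.**

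- All 40 blocks filled: 40 × 1.5 = 60 of 200, the maximum.
- Even spread over 14 teams: 200/14 = 14.3, so ten teams of 14 and four of 15. A team of 14 has two full blocks and four draws of a third: 2 × 1.5 + (0 + 0 + 0.10 + 0.40) = 3.5. A team of 15 has 3 × 1.5 = 4.5. Total: 10 × 3.5 + 4 × 4.5 = 53, or 26.5%.

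**Varied blocks.** The same enumeration for a 6:4 block of ten gives 6/5 + 4/7 = 1.77 certain draws (17.7%) and 6.84 correct guesses (68.4%). With equal numbers of filled blocks of 5 and 10, and an observer who knows each block's size:

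- certain: (1.5 + 1.77)/15 = 21.8%;
- correct guesses: (3.6 + 6.84)/15 = 69.6%.

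Both are upper bounds; they fall when the sizes are hidden.

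**The case against.** The strongest reply is about who has the knowledge and what can be done with it.

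- **Clinicians' knowledge.** Nothing says that teams are told the block size, and a clinician who knows the arms of their own clients does not thereby have the whole team's tally. This stands: for clinicians the figures are an upper bound. They could still infer the pattern, since five lots recur in a stratum of about 14 clients. The objection does not help with the allocator.
- **Control over timing.** Researchers screen every caseload, and clinicians are supposed to ask all selected clients. The client's interest, a research contact, consent and the baseline interview all lie between the approach and the allocation. This also stands: hitting one particular slot is hard. The approach nevertheless comes before consent, and the article does not claim that these steps prevent preference.
- **Batch allocation.** The wording could mean that several clients of a team are allocated together, which would suit a group programme and remove most of the foresight. The text does not settle this, so the one-at-a-time reading is an assumption.
- **Size of the harm.** If the fear is favoured clients meeting a known IMR slot, the relevant share is 20% (at most 40 of 200), not 30%. That is correct.
- **Envelope details.** Sealing may be described in the full protocol. The point does not depend on it: when the remaining lots follow from those already used, a sealed envelope hides nothing.

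A reader might also infer that the principal investigator's work on fidelity (IMR model fidelity section) makes the allocation biased. The documents do not support that. Fidelity is measured after allocation, and rating it is no route to selecting clients.

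**Conclusion.** The article states one block size of five within each team and an allocator who is not described as independent of the trial. That is a design rule as written, not a detail left out, and it leaves a selection route that could easily be narrowed. Under one-at-a-time draws, the principal investigator can be certain of 30% of allocations in filled blocks (about 53 of 200 with an even spread over teams, at most 60) and can guess 72% against 60%. For referring clinicians these figures are a ceiling.

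A reader might infer that clinicians can foresee 60 allocations and steer favoured clients into IMR, or that the trial is open throughout. Neither follows: clinicians' knowledge of the block size is not documented, 60 requires every block to be filled, and the follow-up interviewers are blinded. Nor is there evidence that allocation will be subverted. This is a cheap improvement to the allocation procedure and does not show that the comparison is invalid.

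**What to change.** - Generate the list from the same source with 3:2 blocks of 5 and 10 in random order within each team.
- Do not disclose the block sizes to the teams or the principal investigator.
- Have an existing staff member with no part in recruitment or interviews release each allocation after that client's baseline interview is logged.
- If clients are in fact to be allocated in batches, say so, because that largely removes the foresight.

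The ratio, the team strata and the sample size stay as they are. By the calculation above, certain allocations fall from 30% to at most 21.8% and correct guesses from 72% to at most 69.6%. The gain from block sizes alone is modest for someone who knows them, so non-disclosure and the separate allocator matter at least as much.

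The cost is a new list, a reassigned clerical task and somewhat more within-team imbalance when a block of ten is left incomplete, since teams average about 14 clients. After n draws from a block of N at 3:2, the variance of the IMR count is 0.24 × n(N − n)/(N − 1). The worst-case SD rises from √(0.24 × 6/4) = 0.60 clients (N = 5, n = 2 or 3) to √(0.24 × 25/9) = 0.82 clients (N = 10, n = 5) per team.

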### Statistical analysis

The analyses will be based on the intention-to-treat principle. Generalized linear mixed models will be used to investigate group difference between the experimental and control conditions [52, 53], with times of measurement nested within study participants. As well as the main effects of time and condition, we will investigate whether there is a time x condition interaction effect with respect to symptoms, health complaints, number of relapses and recovery. Because number of relapses is a count variable, the analysis will use a mixed model for the poisson or negative binomial distribution. We will also test whether the addition of a random effect for the time variable results in a better model fit in each of the analyses. For the recovery outcome, we will investigate the influence of illness management, symptoms, relapses and progress on personal goals, as well as their interaction with time. Akaike’s Information Criterion (AIC [54]) will be used for statistical model selection in these analyses.

To explore associations between illness-management outcomes and recovery outcomes, we will use structural equation modelling. To investigate the associations between improvement of symptoms, recovery and fidelity (within IMR + CAU), linear mixed models will be used, with clients nested within IMR groups. As well as a fixed effect for the trainer’s fidelity score, a random intercept at the group level will be incorporated. Before testing the first and second primary hypotheses, we will test the fourth secondary hypothesis: ‘we expect that any improvement resulting from IMR + CAU will be associated with the fidelity with which IMR is implemented.’ If fidelity has an effect, it will be included as a covariate in the subsequent analyses.

Clients will be classified as completers of the study if they have finished all three interviews. After the intention-to-treat analyses, we will perform secondary analyses to measure the effects in clients who have completed IMR.

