#### Intervention

In essence, IMR is a structured training consisting of 11 modules, practitioner guides and handouts for participants. The 11 modules are 1.) Recovery Strategies, 2.) Practical Facts about Mental Illness, 3.) Stress-Vulnerability Model, 4.) Building Social Support, 5.) Using Medication Effectively, 6.) Drug and Alcohol Use and Treatment Strategies, 7.) Reducing Relapses, 8.) Coping with Stress, 9.) Coping with Problems and Persistent Symptoms, 10.) Getting Your Needs Met in the Mental-health System, and 11.) Health for You.

The IMR training will be given at the participating institutes in a group format with weekly sessions. The original American text [19] has been translated into Dutch and will be adapted to the Dutch context if necessary.

During the first module, participants will decide which personal goals they want to work on during the programme. For the first half of each 90-min session, some will work on their goals in the group. During the second half, all participants will work with the help of the handouts on the subjects of the modules.

Our pilot study showed that most modules will require an average of three to four sessions. Each IMR group will be guided by two trainers, who will use 1.) motivation-enhancement strategies such as conveying confidence and exploring the pros & cons of change; 2.) educational strategies (psycho-education) such as interactive teaching, breaking down information, and checking for understanding; and 3.) cognitive-behavioural techniques such as shaping, modelling and role playing. Peer-group support and coping & social skills training are integral to IMR. Homework assignments will be provided. Workbooks and homework assignments can be accessed through an e-health module.

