### Limitations

Firstly, no structured diagnostic interview will be used to confirm the DSM-IV diagnosis. Practical considerations underlay our choice of the clinical diagnosis reported by clinicians on the basis of the medical records; due to the limited relevance of a DSM-IV diagnosis to the present study, this seems to be sufficient.

Another limitation is the chance of recruitment bias. As we consider clinicians to be responsible for treatment, it will be they who suggest that particular clients participate in IMR, and who inform these clients about the study. Although an interview with an assistant researcher will be used to screen all clinicians’ total caseloads for their potential suitability for IMR, and although the clinicians are indeed supposed to ask all selected clients to participate in IMR and to inform them about the study, some clinicians may prefer certain clients for participation in IMR—those whose functioning is better, for example. Some of these selected clients are therefore likely to participate in this study. We will explore which criteria the clinicians use to select participants for IMR.

A further limitation is that the clinicians who score two questionnaires will not be blind for the condition. On the other hand, they will not be involved in the IMR training. Neither, due to the use of self-score questionnaires, will they be blind for the clients.

The use of multiple scales to assess aspects of objective and subjective recovery is a limitation, as multiple testing may introduce positive findings. However, given the comprehensive nature of the IMR model and training programme, we felt that it would not be enough to use IMR scales alone [23, 24], and that a more comprehensive set of scales was needed.

By limiting the cost-utility analyses to health care consumption alone, we will not be able to include potential reductions in social costs, such as those that might occur if IMR participants manage their symptoms well enough to be able to work. But a full assessment of costs is beyond the scope of this study.

Finally, IMR will be offered in our study in a group format, and will be compared with care as usual, which will largely involve an individual format. Some of the possible effect in a group format may be attributable to peer-group support.

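### The between-arm model has no level for the IMR group, although IMR is delivered in groups and CAU is not; if outcomes correlate within groups, the nominal 5% test runs somewhat above 5%

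*Protocol article*

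**What the plan says.** The Statistical analysis section describes generalized linear mixed models for the comparison of the two conditions, "with times of measurement nested within study participants". The only further random effect it considers for these models is one for time. Later in the same section, for the association of improvement with fidelity within IMR + CAU, clients are nested within IMR groups and "a random intercept at the group level will be incorporated". If fidelity turns out to matter, it becomes a covariate in the later analyses.

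On delivery, the Intervention section says: "The IMR training will be given at the participating institutes in a group format with weekly sessions". It adds: "Each IMR group will be guided by two trainers". The Limitations section notes that IMR "will be compared with care as usual, which will largely involve an individual format", and continues: "Some of the possible effect in a group format may be attributable to peer-group support".

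On strata, the Recruitment procedure says: "Participants will be recruited from 14 community mental health teams at 11 branches of two mental health institutions". The Randomisation section says: "Randomisation will be stratified by team". Team does not appear in the Statistical analysis section. The Sample size section states no allowance for clustering.

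**The concern.** Clients in the same IMR group share trainers, sessions and peers for a long programme, at least 8 months in the pilot. Their outcomes may therefore be more alike than those of clients in different groups. This happens in one arm only, so the design is partially nested.

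The plan itself gives grounds to expect between-group variance. It concedes a possible peer-group effect, and its fourth secondary hypothesis is that improvement follows fidelity, which belongs to the group and its trainers. It also models the group level where fidelity is studied, but not where the effect of IMR is tested.

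A positive group correlation that the model ignores makes the standard error of the IMR effect too small. The type I error then exceeds 5% and confidence intervals are too narrow. That bears on the claim of effectiveness and on the guideline recommendation that the Discussion envisages.

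**Working it through.** **The plan's own figure.** The Sample size section gives 74 per arm (148) for d = 0.40, power 0.80, alpha 0.05 (taken as two-sided), 1:1, three measurements. With n per arm = 2f(1.96 + 0.84)²/d²:
- f = 1 (a single endpoint) gives 98.1, so 99 per arm (198 in total);
- f = 0.75 gives 73.6, so 74 per arm (148 in total), which is the stated figure.

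The factor f = 0.75 is an assumption. It follows, for example, from a within-client correlation of 0.5 and the mean of two follow-ups, (1 + 0.5)/2. The stated 148 thus agrees with a client-level calculation with no design effect.

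**Inputs for the check.** 120 IMR and 80 CAU clients (Randomisation) and 14 teams (Recruitment procedure). Assumed, because the documents do not say: one IMR group per team, so m = 120/14 = 8.57; and a group ICC of 0.02, 0.05 or 0.10 on the client-level contrast being tested.

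**Formulae.**
- Design effect in the IMR arm: DE = 1 + (m − 1) × ICC.
- True variance over model variance: R = (DE/120 + 1/80)/(1/120 + 1/80) = 0.6 + 0.4 × DE.
- Actual type I error: 2 × [1 − Φ(1.96/√R)].

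| Group ICC | DE | R | SE ratio √R | Type I error |
|---|---|---|---|---|
| 0 | 1.00 | 1.00 | 1.00 | 5.0% |
| 0.02 | 1.15 | 1.06 | 1.03 | 5.7% |
| 0.05 | 1.38 | 1.15 | 1.07 | 6.8% |
| 0.10 | 1.76 | 1.30 | 1.14 | 8.6% |

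Over a wider assumed range (groups of 6 to 10, ICC 0.01 to 0.10) the result runs from 5.2% to 9.3%. Null simulations of 20,000 trials per setting agree: 6.6% against 6.6% by formula for groups of 8 at ICC 0.05, and 9.1% against 9.3% for groups of 10 at ICC 0.10.

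**Treatment drop-out.** The Randomisation section expects up to 50% drop-out from treatment in the IMR arm and calls this pessimistic. As a bounding case, let 60 of the 120 share no group exposure and the other 60 sit in 14 groups of 4.29. The average DE is 1 + 0.5 × 3.29 × ICC = 1.03 / 1.08 / 1.16, and the type I error is 5.2% / 5.4% / 5.8%. Clients who leave late keep some shared exposure, so the truth would lie between these figures and those in the table.

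**Team left out.** Stratified allocation balances team effects between the arms, but a model without team keeps their variance in the error. Alone, this gives R = 1 − team ICC: about 4.4% at team ICC 0.05 and 3.9% at 0.10. With both terms omitted, R = 0.6 + 0.4 × DE − team ICC:

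| Group ICC | Team ICC 0.05 | Team ICC 0.10 |
|---|---|---|
| 0.02 | 5.1% | 4.6% |
| 0.05 | 6.2% | 5.6% |
| 0.10 | 8.0% | 7.4% |

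**Power of a test with the correct standard error**, at 120:80 and f = 0.75, with all 200 analysed: Φ(0.40/√[0.75 × (DE/120 + 1/80)] − 1.96). This gives 89% without clustering and 87% / 85% / 80% at ICC 0.02 / 0.05 / 0.10. For groups of 10 at ICC 0.10 it is 78%. With f = 1 the unclustered figure would be 79%, so these power figures depend on the assumed factor.

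**The case against.** **The size is unknown.** The documents give no ICC, group size or number of groups, and at ICC zero the planned model is correct. This stands: it is too strong to say that the standard errors are wrong. They may be too small.

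**Two omissions pull in opposite directions.** A reader might infer that leaving out group and team both inflate the error. Leaving out team is conservative. This stands, and the net figures above show it. The offset cannot be relied on, though: it depends on two unrelated correlations, and the net result runs from 4.6% to 8.0% over the assumed values.

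**Team may be in an analysis plan that is not shown.** An article may well leave adjustment for strata to that plan, so the silence on team is not a defect in itself. Team matters here only for the net size and because it belongs in the same model. The group level is different. The article names the levels of the between-arm model and assigns the group intercept to another analysis. That wording does not strictly exclude a further level, but it points away from one.

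**Fidelity may enter as a covariate.** It could absorb some between-group variance. But its inclusion depends on a prior test, it is defined only for IMR clients, and it leaves the remaining group variance unmodelled.

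**The trial might seem underpowered.** A reader might infer this from the absent clustering allowance. The documents do not support it. The plan randomises 200 against a calculated 148, and under the variance factor that reproduces 148, power stays at about 80% to 87% over the ICC range at 8.6 clients per group.

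**Conclusion.** The concern holds in a conditional form. The between-arm model as described does not match a design in which one arm is treated in groups. With about 8.6 clients per group and a group ICC of 0.02 to 0.10, both assumed, the nominal 5% test would run at about 5.7% to 8.6%. The excess shrinks to 0.2 to 0.8 percentage points if half the IMR clients share no group exposure, and vanishes at ICC zero. Omitting team lowers these figures by an amount that cannot be known beforehand; for example, about 6.2% remains at group ICC 0.05 and team ICC 0.05. What is at risk is type I error and interval coverage. No power shortfall is shown, given the assumed variance factor of 0.75 and all 200 clients analysed.

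**What to change.** For the primary and secondary between-arm comparisons, replace the stated nesting with a partially nested mixed model:
- a random IMR-group effect in the IMR arm only, and a group-by-time effect if it can be estimated, because the hypotheses concern a condition by time interaction;
- each CAU client as a singleton;
- small-sample degrees of freedom (Satterthwaite or Kenward-Roger) where the model allows, since the number of groups will be small;
- team as a stratification factor.

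Under intention-to-treat, state which group a client belongs to who leaves or never attends, for instance the group to which the client was assigned. Settle the wording before any unblinded outcome data are seen, and report the estimated group ICC with the result.

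The cost is a few sentences in the Statistical analysis section. Group membership is already needed for the fidelity analysis, and team is known from randomisation. No extra data and no change in sample size are needed. The downside is slightly wider confidence intervals.

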### Hypotheses

We have two primary hypotheses and four secondary hypotheses. The first primary hypothesis is that IMR + CAU (IMR offered in group format) leads to better illness management and to fewer symptoms and relapses than CAU only. The second primary hypothesis is that IMR + CAU leads to better ‘subjective’ and ‘objective’ recovery than CAU only. We thus expect a condition x time interaction effect of the IMR + CAU group over the CAU-only group.

The first secondary hypothesis is that the cost-utility of IMR + CAU is better than that of CAU.

We intend to explore the working mechanisms of IMR by testing the second secondary hypothesis that better illness management (i.e. getting greater psychiatric insight, better coping, more social support, less addiction and better service engagement) leads to fewer symptoms and relapses. We also intend to test the third secondary hypothesis that better ‘distal outcomes’ (i.e. recovery, see Fig. 1) result from a combination of better ‘proximal outcomes’ (i.e. better illness management and fewer symptoms and relapses) and progress on personal goals [2]. Finally, we expect that any improvement resulting from IMR + CAU will be associated with the fidelity of IMR implementation (fourth secondary hypothesis).

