## Design

This research project entails a randomised controlled trial in which clients who provide written informed consent will be assigned to the experimental condition (IMR) or the control group. The experimental group will consist of clients who participate in the IMR programme (which will be offered in a group format) and also get CAU. The control group will receive CAU.

Measurement is planned to take place before randomisation and at 12 and 18 months after randomisation.

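### Testing IMR through time × condition with a free baseline mean in each arm gives up precision that the pre-randomisation measurement offers at no cost

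*Protocol article*

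**What the plan says.** All places are in the protocol article.

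- **Design:** "Measurement is planned to take place before randomisation and at 12 and 18 months after randomisation". Recruitment procedure confirms the order: consent, then baseline interview, then randomisation.
- **Hypotheses**, after the two primary hypotheses: "We thus expect a condition x time interaction effect of the IMR + CAU group over the CAU-only group".
- **Statistical analysis:** mixed models with occasions nested within participants. "As well as the main effects of time and condition", the time × condition interaction is to be examined. That sentence names symptoms, health complaints, relapses and recovery; it does not name the self-rated IMRS.
- **Sample size**, for the self-rated IMRS: "we anticipate a medium effect size of 0.40 on the primary outcome variable", based on "power analyses with three times of measurement (mixed models), equal allocation to the experimental and control groups". Baseline is thus counted as an outcome occasion for the primary outcome too.
- **Covariates:** no common baseline mean and no baseline covariate appears anywhere. The only covariate named for the treatment comparison is fidelity, if it proves to have an effect.

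**The concern.** Because baseline precedes randomisation, any baseline difference between the arms is chance. A model with a free condition effect at baseline ignores this. It estimates the chance difference and, through the interaction, subtracts all of it from the follow-up difference. A model with one baseline mean for both arms, or with baseline as a covariate, subtracts only the part that the within-person correlation warrants. For continuous outcomes in a linear model, its large-sample variance is never larger. What is at stake is the width of the confidence intervals and the power for the self-rated IMRS and the many continuous secondary scales.

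**Working it through.** **Inputs.** Effect size 0.40 (SD taken as 1), power 0.80, alpha 0.05: "a power of .80, alpha at 0.05, and an effect size of .40" (Sample size). Alpha is taken as two-sided, since the article does not say. Arms: "120 to the experimental condition and 80 to the CAU group" (Randomisation). The within-person correlation ρ is not in the documents, so I assume the same ρ between all occasions and show 0.3 to 0.7. Follow-up is assumed complete, because no figure is given for loss of measurements.

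**The plan's own figure.** The Sample size section concludes that "it will be necessary to randomize 148 clients: 74 to the experimental condition and 74 to the CAU group". With a variance factor f for the estimator,

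n per arm = 2f(1.960 + 0.842)² / 0.40² = 98.1 f.

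With f = 1 this gives 99 per arm (one-sided, 78), not 74. A result of 74 needs f = 74/98.1 = 0.754. At ρ = 0.5 three different estimators have f = 0.75, and 98.1 × 0.75 = 73.6, i.e. 74:

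- change to the mean of both follow-ups: 1.5(1 − 0.5)
- baseline-adjusted single follow-up: 1 − 0.5²
- mean of both follow-ups without baseline: (1 + 0.5)/2

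Single-visit change gives the same f at ρ = 0.625, since 2(1 − 0.625) = 0.75. So 148 is plausible, but it does not reveal which estimator or ρ lay behind it.

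**Variance factors.**

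- One follow-up: change 2(1 − ρ); shared or adjusted baseline 1 − ρ². Their ratio is 2/(1 + ρ), which is never below 1.
- Mean of both follow-ups: change 1.5(1 − ρ); shared or adjusted baseline (1 + ρ)/2 − ρ².

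| ρ | One visit: change | adjusted | variance falls by | Mean of two: change | adjusted | variance falls by |
|---|---|---|---|---|---|---|
| 0.3 | 1.40 | 0.91 | 35% | 1.05 | 0.56 | 47% |
| 0.5 | 1.00 | 0.75 | 25% | 0.75 | 0.50 | 33% |
| 0.7 | 0.60 | 0.51 | 15% | 0.45 | 0.36 | 20% |

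Below ρ = 0.5 the single-visit change factor exceeds 1, so it is less precise than ignoring baseline altogether.

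**Power at 120/80.** 1/120 + 1/80 = 1/48, so SE = √(f/48) and power = Φ(0.40/SE − 1.96). Example at ρ = 0.5, one visit:

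- Change: SE = √(1.00/48) = 0.144; 0.40/0.144 = 2.77; Φ(0.81) = 79%.
- Adjusted: SE = √(0.75/48) = 0.125; 0.40/0.125 = 3.20; Φ(1.24) = 89%.

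| ρ | One visit: planned | shared baseline | Mean of two: planned | shared baseline |
|---|---|---|---|---|
| 0.3 | 65% | 83% | 77% | 96% |
| 0.5 | 79% | 89% | 89% | 97.5% |
| 0.7 | 95% | 97% | 98.5% | 99.6% |

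In sample-size terms at ρ = 0.5, 1:1 and 80% power, one visit needs 198 clients by change and 148 with the shared baseline. The mean of both visits needs 148 and 100.

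**Check by simulation** (120/80, ρ = 0.5, complete data, 300 trials). The 18-month interaction from a mixed model with categorical time equalled the raw difference in mean change to within rounding error. Mean SEs were 0.144 unconstrained and 0.125 with a common baseline, as the formulas give. Simulated power was 78% and 85%. The latter is somewhat below the analytic 89%, and 300 trials are few, so I rely on the formulas.

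**The case against.** The planned test is a standard one. Under randomisation it is unbiased and keeps its type I error, so nothing here is an error in the strict sense. All of that stands: the point concerns precision, not validity.

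It can also be said that baseline handling is a detail an article leaves to the analysis plan. That would hold if the article were silent. It names the model terms and makes the interaction the expected effect, so the proposal changes a stated method.

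Three limits stand:

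- The exact identity with change from baseline needs categorical time and complete data, and the article does not state the time coding. Linear time would also leave separate baseline intercepts and the same kind of loss, but the factors above would not apply as they are.
- The sentence in Statistical analysis does not name the self-rated IMRS. Its inclusion is an inference from Hypotheses and Sample size, though a strong one.
- The gain depends on an unknown ρ and shrinks as ρ rises. At 0.8 the single-visit variance falls by only 10% (1 − 0.36/0.40).

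A reader might go further and infer that the trial's power is below the stated 80%. The documents do not support that. The planned contrast on the mean of both visits reproduces 74 per arm at ρ = 0.5, and the trial randomises 200, not 148. The 50% drop-out in Randomisation is from treatment, not from measurement.

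**Conclusion.** The point holds as a free improvement. As described, the model estimates a baseline difference that randomisation has already set to zero in expectation, and pays for it in precision. Under equal correlations of 0.3 to 0.7, a shared or adjusted baseline lowers the variance by 35% to 15% for one visit and by 47% to 20% for the mean of both. The power gain at 120/80 is large at low correlation (65% to 83% for one visit at 0.3) and small at high correlation (95% to 97% at 0.7). These figures rest on an assumed ρ, categorical time, complete follow-up and an effect of 0.40.

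The conclusion covers the continuous outcomes. It does not extend to the relapse count, where the interaction is a ratio of rate ratios and the comparison with change scores is only an analogy.

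**What to change.** For the self-rated IMRS and the other continuous outcomes, replace the free condition main effect plus interaction with one of two equivalent routes:

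- keep baseline as an outcome, with time categorical, a common baseline mean for both arms (no condition effect at baseline), and condition effects at 12 and 18 months; or
- model the two follow-up visits with baseline as a covariate.

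Report the condition differences at 12 and 18 months with confidence intervals as the treatment effect, and reword the expected effect in Hypotheses to match. The cost is analysis wording, settled before outcome data by arm are seen. No new data are needed, since baseline is already collected before randomisation.
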